### Sample size {14}

We used the results of the CRISP trial to inform our sample size calculations for this trial (paper under review, *Med. J. Aust.*). The original sample size of 218 participants for the grant application was based on a 20% difference between the intervention and control arms, assuming 25% in the control arm and 45% in the intervention arm, with 10% attrition at 12 months. However, in the CRISP trial, we found 40% had risk-appropriate screening in the control arm and 60% in the intervention arm of those due screening at 12 months for participants aged 50 years and older. The primary outcome had less than 5% missing data as it was derived from multiple data sources (such as GP record, Victorian Admitted Episodes Dataset (VAED), Medicare Benefits Schedule (MBS), the National Bowel Cancer Screening Program (NBCSP)) and did not rely only on self-report from a returned questionnaire. Furthermore, our original sample size calculation assumed all participants would be due a CRC screening test, as would be expected for participants aged above 50 years old based on current guidelines and the eligibility criteria. However, for participants aged 45 to 49 years, appropriate screening will be defined as no CRC screening if classified as having average CRC risk and iFOBT if they are classified as moderate CRC risk. Hence, to ensure that we had sufficient power to detect a difference appropriate CRC screening between the arms, we revised our sample size to allow for an attenuation in the intervention effect, explained as follows.

We estimated that 25% of the trial sample will be aged 45–49 years old, of which 90% will be at average risk and 10% at moderate risk [50]. We conservatively assumed that 95% of those aged 45 to 49 years in the average risk group will be appropriately screened in both trial arms (i.e. no CRC screening); those identified as moderate risk, we assumed that 70% in the intervention arm and 10% in the control arm would be appropriately screened (i.e. iFOBT screening). Thus, for those aged 45–49 years, the expected between-arm difference in appropriate screening would be 6% (92.5% intervention vs 86.5% in the control arm). We also assumed that for participants aged 50 years and older who were due a CRC screening test in the next 12 months, 60% would be appropriately screened in the intervention arm and 40% in the control arm (paper in submission).

Thus, we revised the sample size to detect a between-arm difference of 17% (68% vs 51%, after taking a weighted average of the proportions aged above or below 50 years). To detect this effect size, with 80% power and a two-sided 5% significance level, we require a total sample size of 274 participants at baseline (137 participants per arm), allowing for 5% of the primary outcome data to be missing.

This is an additional 56 participants to the trial from the original sample size calculations provided in the grant proposal and Trials registry. This sample size also provides 90% power (5% significance level) to detect a 20% between-arm difference for appropriate screening for participants aged 50 years and older (60% in the intervention and 40% in the control group, 5% missing data).

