## Assignment of interventions: allocation

### Sequence generation {16a}

Participants will be randomly allocated 1:1 to the intervention or control arms. The allocation sequence will be computer-generated stratified by general practice using permuted blocks of random sizes. To ensure concealment, the block sizes will not be disclosed. Using restricted randomisation within the stratum ensures that the number of individuals is balanced between study arms.

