## Data collection and management

### Plans for assessment and collection of outcomes {18a}

#### Primary outcome

The primary outcome is the proportion of participants who have had risk-appropriate CRC screening at 12 months’ follow-up. The appropriate type and frequency of screen will be determined by participant’s level of CRC risk as follows:

For those aged 50 years and over:*Average-risk category*: for participants whose 10-year absolute risk of colorectal cancer is less than 4% based on their PRS, family history, age and sex (intervention only) and who do not fall into the moderate risk category of the 2017 NHMRC-endorsed Australian guidelines [5] (both trial arms), iFOBT every 2 years is considered risk-appropriate screening.*Moderate-risk category*: for participants whose 10-year absolute risk of colorectal cancer is greater than or equal to 4% based on their PRS, family history, age and sex (intervention only), or they had a self-reported family history of CRC (both trial arms) that places then in the moderate risk category of the 2017 Australian guidelines [5], risk-appropriate screening is colonoscopy every 5 years.

For those aged under 50 years:*Average-risk category*: for participants whose 10-year absolute risk of colorectal cancer is less than 1% based on their PRS, family history, age and sex (intervention only) and do not fall into the moderate risk category of the 2017 NHMRC-endorsed Australian guidelines [25] (both trial arms), risk-appropriate screening is no screening until aged 50 years.*Moderate-risk category*: for participants whose 10-year absolute risk of colorectal cancer is greater than or equal to 1% based on their PRS, family history, age and sex (intervention only), or they had a self-reported family history of CRC (both trial arms) that placed then in the moderate risk category of the 2017 Australian guidelines [5], risk-appropriate screening is iFOBT every 2 years until aged 50 years.

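### The 80% power at 274 participants rests on a 17-point difference; the plan's own inputs give 16.5 points and about 78% power, and that is an upper bound under its outcome rule

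*Protocol article*

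**What the plan says.** All of the power inputs are in Sample size {14} of the protocol article.

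- Age mix and risk split: "We estimated that 25% of the trial sample will be aged 45–49 years old, of which 90% will be at average risk and 10% at". The 10% here is the moderate-risk group. A single split is given, with no distinction by arm.
- Success rates at age 45–49: 95% in both arms for average risk, where success means no screening. For the rest, "those identified as moderate risk, we assumed that 70% in the intervention arm and 10% in the control arm would be appropriately screened".
- Result at age 45–49: "the expected between-arm difference in appropriate screening would be 6% (92.5% intervention vs 86.5% in the control arm").
- Success rates at 50 and over: 60% intervention, 40% control.
- Target: "Thus, we revised the sample size to detect a between-arm difference of 17% (68% vs 51%, after taking a weighted average of the proportions" in the two age bands).
- Size: "To detect this effect size, with 80% power and a two-sided 5% significance level, we require a total sample size of 274 participants at baseline". That is 137 in each arm and includes a 5% allowance for a missing primary outcome.

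The outcome rule stands elsewhere. Under Outcomes {12}, the control arm's appropriate test is set by family history under the national guidelines. Under Plans for assessment and collection of outcomes {18a}, a person under 50 is moderate risk if 10-year risk is "greater than or equal to 1% based on their PRS, family history, age and sex (intervention only"), or if family history places them there (both arms).

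**The concern.** There are two separate problems in the same calculation.

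First, the printed target is described as a weighted average, but the stated weights and rates do not give the printed control figure of 51%. The sample size is computed from that figure.

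Second, one moderate-risk share is applied to both arms at age 45–49, while the outcome rule classifies the arms differently. A control participant who is moderate by PRS alone is scored as average risk. For that person no screening counts as success, which the plan sets at 95%. The power calculation instead places such a person, if counted in the 10%, in a group with 10% success. That lowers the expected control rate and widens the expected gap.

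The revision was made to allow for a diluted effect in this age group. If the allowance is too small, a null result would be read against 80% power that the plan's own inputs do not give.

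**Working it through.** **Inputs from the plan.** Share aged 45–49: 0.25. Rates at 45–49: 0.925 and 0.865. Rates at 50 and over: 0.60 and 0.40. Two-sided 5% level, 80% power, 5% missing. Allocation: "Participants will be randomly allocated 1:1 to the intervention or control arms".

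**Step 1. Reproduce 274.** The usual two-proportion formula with pooled variance under the null and no continuity correction is

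n per arm = [1.96·√(2p̄(1−p̄)) + 0.8416·√(p1(1−p1) + p2(1−p2))]² / (p1−p2)².

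With p1 = 0.68, p2 = 0.51, p̄ = 0.595: [1.96·√0.48195 + 0.8416·√0.4675]² / 0.0289 = 129.7, so 130. Then 130/0.95 = 136.8, so 137 per arm and 274 in total. The match is exact, so the formula is sound and 68% vs 51% is what was entered.

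**Step 2. Recompute the weighted average.**

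- Intervention: 0.25 × 92.5 + 0.75 × 60 = 68.125%
- Control: 0.25 × 86.5 + 0.75 × 40 = 51.625%
- Difference: 16.5 points

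The control figure rounds to 52%, not 51%.

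**Step 3. Power at 274 with these values.** Evaluable per arm: 137 × 0.95 = 130.15, taken as 130. With p̄ = 0.59875:

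power = Φ{[0.165·√130 − 1.96·√0.4805] / √0.4669} = Φ(0.765) = 77.8%.

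Exact enumeration of the chi-square test gives 77.9%, against 80.3% for 68% vs 51%. For 80% power the formula gives 137.3 evaluable per arm. Dividing by 0.95 gives 144.6, so 145 per arm (290). Rounding up to 138 first gives 145.3, so 146 per arm (292).

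**Step 4. Let the moderate-risk shares at 45–49 differ by arm.** Write x for the control share (family history only) and y for the intervention share (family history or PRS risk of 1% or more). With the plan's success rates:

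- Control rate: 0.95(1−x) + 0.10x = 0.95 − 0.85x
- Intervention rate: 0.95(1−y) + 0.70y = 0.95 − 0.25y
- Gap at 45–49: 0.85x − 0.25y
- Overall difference: 0.25 × gap + 0.75 × 0.20

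With x = y = 0.10 this returns the plan's 6 points and 16.5 overall. Randomisation makes the family-history share the same in expectation, so y is at least x, with equality only if the PRS reclassifies nobody. Whether 10% is the control share (y rises above it), the intervention share (x falls below it) or an average of the two, the gap cannot exceed 6 points. Hence 77.8% is the ceiling.

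**Step 5. Illustrations.** The plan does not state arm-specific shares. Every row after the first is an assumption. Power is at 130 evaluable per arm.

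| Control x / intervention y | Gap at 45–49 (points) | Overall difference (points) | Power |
|---|---|---|---|
| 10% / 10% (plan) | 6.0 | 16.5 | 78% |
| 10% / 12% | 5.5 | 16.4 | 77% |
| 8% / 10% | 4.3 | 16.1 | 76% |
| 10% / 20% | 3.5 | 15.9 | 74% |
| 5% / 10% | 1.75 | 15.4 | 72% |
| 0% / 10% (extreme) | −2.5 | 14.4 | 66% |

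**The case against.** The best defence is that the power statement is conditional. For 68% vs 51%, 274 participants do give 80%. The slip is half a point on inputs that the plan itself presents as estimates, and 16.5 can be rounded to 17. That is fair as to size: the slip alone costs about 2 points of power and 16 to 18 participants. It does not rescue the text, because the target is said to be the weighted average of listed rates and those rates do not give 51%.

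On the second part, the 10% comes from a cited source that is not shown, and the article does not say whether it is by PRS, by family history or for the whole sample. A reader might infer that true power is 66%, or lies in the high 60s to low 70s. The documents do not support that. The 66% case needs no control aged 45–49 to be moderate by family history, yet the eligibility criteria exclude only a known genetic predisposition or a family history that needs genetic referral, so moderate histories can enter. Small differences between the arms' shares leave power at 76–77%. Only the direction follows from the outcome rule.

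A reader might also infer that the trial's inference is unsound. It is not: the analysis model, the type I error and the validity of the estimate and its interval are untouched. The 60% vs 40% assumption for the older 75% of the sample, which drives most of the power, is not challenged here.

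**Conclusion.** The concern holds in two parts of different certainty.

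Certain, from the plan's own figures: the weighted average is 68.1% vs 51.6%, the difference is 16.5 points, and power at 274 is about 78%, not 80%.

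Certain in direction only: the common 10% moderate-risk share conflicts with the arm-specific outcome rule unless the PRS moves nobody aged 45–49 into the moderate category. The 6-point gap and the 78% are therefore upper bounds. This rests on the plan's success rates (95%, 70%, 10%) and on the 10% describing one arm's share or an average of both.

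How far below 78% the power lies cannot be settled from the documents. The illustrations run from 77% for a slight difference in shares to 66% at the extreme, and none should be quoted as the trial's power.

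**What to change.** In Sample size {14}:

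1. Replace the target with 68.1% vs 51.6% (16.5 points), and state power at 274 as at most about 78%.
2. Say whether the 10% moderate-risk share at age 45–49 is by PRS, by family history or for the whole sample.
3. Recompute the 45–49 rates with separate moderate-risk shares for each arm that follow the outcome rule in {12} and {18a}, and report the resulting difference and power as a sensitivity range below 78%, with the assumed shares labelled as such.

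The cost is a rewritten paragraph and a less favourable stated figure. No extra enrolment is asked for, and neither the outcome definition nor the analysis changes.

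### The 90% power stated for participants aged 50 and older counts all 274 participants; on the plan's own 75% share, the expected power is about 80%.

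*Protocol article*

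**What the plan says.** All the relevant statements are in the Sample size section of the protocol article, apart from the allocation ratio.

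- Age mix: "We estimated that 25% of the trial sample will be aged 45–49 years old". The other 75% are therefore 50 or older.
- Planning rates for the older group, among those due a test: "60% would be appropriately screened in the intervention arm and 40% in the control arm".
- Blended target for the whole sample: "between-arm difference of 17% (68% vs 51%, after taking a weighted average of the proportions aged above or below 50 years").
- Resulting size: "we require a total sample size of 274 participants at baseline (137 participants per arm), allowing for 5% of the primary outcome data to be" unavailable.
- Error rates behind that size: "with 80% power and a two-sided 5% significance level".
- The further claim: "This sample size also provides 90% power (5% significance level) to detect a 20% between-arm difference for appropriate screening for participants aged 50 years" or above. The rates for it are given in brackets as "60% in the intervention and 40% in the control group, 5% missing data".
- Sequence generation sets 1:1 allocation.

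The section does not reduce the 274 to the part expected to be 50 or older before making the further claim. It also does not say that the claim supposes every participant to be in that age group.

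**The concern.** The two power statements use one sample size but treat its age mix differently. The first blends two age groups in a 75:25 ratio. The second concerns only the larger group, yet it appears to keep the full number.

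The older group is where the plan expects the effect. The section assumes a difference of 20 points at 50 and older and 6 points at 45–49. Weighted by share, the older group contributes 0.75 × 20 = 15 points to the blended difference and the younger group 0.25 × 6 = 1.5 points. The 60% and 40% also come from the earlier trial's participants of this age, so this is the comparison that readers will set beside that trial.

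If the power is overstated, a null finding in this group will look like stronger evidence against an effect than the design can supply. The sentence also presents 90% power as a benefit of the enlarged sample, which the expected sample does not deliver.

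**Working it through.** **Inputs**, all from the Sample size section except the ratio: 274 in total, 137 per arm, 1:1; 5% missing; two-sided 5%; 60% against 40% at 50 and older; 75% of the sample in that group.

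**Formula** (normal approximation, pooled variance under the null, no continuity correction). With d = p1 − p2 and p̄ = (p1 + p2)/2:

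- n per arm = [z(0.975)·√(2p̄(1−p̄)) + z(power)·√(p1(1−p1) + p2(1−p2))]² / d²
- power = Φ{[d·√n − z(0.975)·√(2p̄(1−p̄))] / √(p1(1−p1) + p2(1−p2))}

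**Step 1: is this the plan's method?** For 68% against 51% at 80% power:

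- √(2 × 0.595 × 0.405) = 0.6942 and √(0.2176 + 0.2499) = 0.6837
- n = (1.960 × 0.6942 + 0.8416 × 0.6837)² / 0.17² = 129.7, so 130 per arm
- 260 / 0.95 = 273.7, so 274. This matches the plan.

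**Step 2: reproduce the 90%.** For 60% against 40%:

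- √(2 × 0.5 × 0.5) = 0.7071 and √(0.24 + 0.24) = 0.6928
- n = (1.960 × 0.7071 + 1.2816 × 0.6928)² / 0.20² = 129.3, so 130 per arm
- 260 / 0.95 = 273.7, so 274. This matches again, with all 274 counted as 50 or older.
- In the other direction, 274 × 0.95 / 2 = 130.15 per arm gives power of 90.2%.

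**Step 3: apply the plan's age share.**

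- Enrolled at 50 or older: 274 × 0.75 = 205.5
- Evaluable: 205.5 × 0.95 = 195.2, or 97.6 per arm
- Power = Φ[(0.20 × √97.6 − 1.960 × 0.7071) / 0.6928] = Φ(0.852) = 80.3%

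**Step 4: can another reading restore 90%?**

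| Variation (75% aged 50 or older unless stated) | Power |
|---|---|
| Unpooled variance | 81.4% |
| Continuity correction | 76.0% |
| Exact power of the chi-square test, 97 to 98 per arm | 81% |
| No missing data (102.75 per arm) | 82.3% |
| One-sided 5%, 5% missing | 88.0% |
| One-sided 5%, no missing data | 89.4% |
| Share 70% | 77.5% |
| Share 80% | 82.8% |
| Share 90% | 86.9% |
| Share 95% | 88.7% |
| Share 100% | 90.2% |

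The share rows use the pooled two-sided formula with 5% missing. Only a share near 100% reaches 90%. The one-sided rows come close, but they depart from the two-sided level set for the main calculation, and the higher of them also drops the 5% missing that the sentence itself states.

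**Size of the gap.** For 90% power at a 75% share, the total would be 260 / 0.95 / 0.75 = 364.9, so 365.

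**The case against.** The best defence is that the sentence was meant as a benchmark. The section recalls that the first calculation took everyone to be due a test. The 90% statement comes straight after the comparison with that first size. The authors may have meant that, if the whole sample behaved like the older group, power would be 90%. The exact agreement at 274 fits that reading as well as it fits a slip. But the sentence carries no such condition and speaks of participants of that age, so on this reading too it needs rewording.

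Three further points stand and limit the consequences:

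- The statement is secondary. The 274 was set by the blended comparison at 80% power, and the primary analysis compares all randomised participants.
- The article specifies no confirmatory test in those aged 50 and older and leaves subgroup analyses to the SAP. The risk of misreading a null result arises only if such an analysis is reported.
- The 25% is an estimate and recruitment is consecutive, so the achieved share may differ. The 80% is the power expected under the plan's assumption, not a fixed property of the trial.

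It is also fair to say that about 80% meets the standard the trial set for its main comparison.

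**Conclusion.** The concern holds. On the plan's own inputs and method, expected power for 60% against 40% among participants aged 50 and older is 80.3%, not 90%. The type II error is 19.7% against the 10% implied.

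This rests on a 75% share in both arms, 5% missing outcomes in this age group as in the whole sample, a two-sided 5% test and the pooled-variance formula. Other two-sided methods give 76% to 81%, and shares from 70% to 90% give 77.5% to 86.9%. The finding concerns this one statement and does not show that the trial is too small for its primary objective.

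**What to change.** Replace the sentence on the older group. Suggested wording: *If 75% of the 274 participants are aged 50 or older and 5% of outcomes are missing (about 195 evaluable), power to detect 60% against 40% in this group is about 80% at the two-sided 5% level.* If the authors wish to keep the 90%, they should say that it holds only if all 274 are in that age group.

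The cost is one sentence in the protocol and a less favourable figure. Enrolment, analysis and the primary calculation are unaffected. The SAP or any other trial document needs the same correction only if it repeats the 90%, which cannot be seen from the article.

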### Recruitment {15}

#### Identification of potential participants and recruitment

Patients aged between 45 and 70 on appointment lists of consented GPs within 1 week of the appointment will consecutively be approached. A consecutive approach is utilised to minimise selection bias and ensure a representative sample. The initial approach of potential participants by researchers will take place in one of two ways: face-to-face in the general practice waiting rooms or via telephone. In the era of COVID-19, community lockdowns have resulted in many GP appointments being moved to telehealth delivery and efforts being made to reduce waiting room traffic [51], we anticipate that eligible patients will mainly be approached via telephone.

#### Initial approach

Potential participants will be approached either in the waiting room or via telephone by a research assistant. Their eligibility will be checked, and they will be given an information sheet about the trial, either in hard copy or via email. Those approached via phone will be given the option to complete their recruitment in person or via teletrial.

#### Face-to-face recruitment

Interested potential participants with upcoming face-to-face appointments will be asked to attend their GP appointment 20 min early to meet with the researcher. Those whose appointments have already passed will be asked to attend their clinic at a convenient time. Confirmation of eligibility and obtaining informed consent in conducted in a private consulting room.

#### Teletrial recruitment

Interested potential participants who opt for teletrial recruitment, or those who cannot attend their clinic for research purposes due to COVID-19 lockdowns, will have the verbal portion of the consent completed over the phone. The study information sheet, consent forms, baseline questionnaire and DNA collection kit will then be posted to them. These participants are not considered enrolled in the trial until the consent form, baseline questionnaire and DNA sample are returned.

#### Ineligible patients and patients who do not wish to participate in the trial

An electronic recruitment log containing age and gender will be kept throughout recruitment. Reasons for ineligibility or refusal (if provided) will be recorded in REDCap. No identifying data will be kept for this group. This recruitment log will be maintained to track the representativeness of the recruited sample.

Two attempts will be made to reschedule non-attendances at recruitment appointments and to remind those who have received recruitment documents in the post, after which these potential participants will be marked as refused and their identifying information will be destroyed.

## Assignment of interventions: allocation

### Sequence generation {16a}

Participants will be randomly allocated 1:1 to the intervention or control arms. The allocation sequence will be computer-generated stratified by general practice using permuted blocks of random sizes. To ensure concealment, the block sizes will not be disclosed. Using restricted randomisation within the stratum ensures that the number of individuals is balanced between study arms.

